#### Proxy measures

The following measures will be detailed by the respective caregiver of each participant: The CATS-2 caregiver version [26] which comprises the same items as the CATS self-report with a reference to the child/adolescent (“has your child…”).

One item derived from the Nation Outcome Scales for Children and Adolescents (HoNOSCA) [28] will be used to obtain a proxy estimation of substance abuse.

The CAMHSRI-DE [28] is an interview tool for the assessment of medical and psychosocial services used by children and adolescents with mental health problems based on the European version CAMHSRI-EU [40]. Service costs will be estimated by combining service use assessed by the CAMHSRI-DE with unit costs gathered from a broad spectrum of information sources. The CAMHSRI-DE will be adapted for refugee youths (CAMHSRI-REF) and will be administered by the caregiver in collaboration with the UYR.

#### Long-term follow-up sub-sample

A subsample of *n* = 100 will be assessed with additional questionnaires and will be followed up for 18 (T3) and 24 months (T4). The short version of the Group Climate Instrument for Children (GCIC) [41] consisting of 14 items assessing open and closed climate in institutions will be used. This questionnaire showed good to moderate reliability for the open (Cronbach’s *α* = 0.91) and the closed scales (Cronbach’s *α* = 0.71). It has been validated in the context of residential care in different countries [41, 42].

The Brief Acculturation Orientation Scale (BAOS) [43] is a bidimensional instrument assessing the acculturation orientation towards the home country and the host country independently. The home and host country factors of the BAOS showed acceptable reliability (Cronbach’s *α* = 0.72–0.78).

The Brief Sociocultural Adaptation Scale (BSAS) [43] is a 12-item questionnaire that assesses various aspects of sociocultural adaption (e.g., language, climate, people, values, and beliefs). The scale demonstrated good reliability (Cronbach’s *α* = 0.85); it is available and has been validated in different languages.

The questions on social support are based on the Social Support Questionnaire (SSQ6-G) [44]. In its original version, the three scales showed good reliability (Cronbach’s *α* = 0.71 to 0.92).

The Daily Stressors Scale for Young Refugees (DSSYR) [45] examines the extent to which 15 different post-migration daily stressors were experienced by the participants during the previous month.

#### Measures for “Mein Weg” trainers and TF-CBT therapists

Both groups of professionals will complete questionnaires before and after the training (therapists also before the online training) as well as 6 and 12 months post-training. The Professional Quality of Life (ProQOL) is a 30-item questionnaire that measures the negative and positive effects of helping others who experience suffering and trauma [46]. The items form 3 subscales corresponding to compassion satisfaction (*α* = 0.89–0.91), burnout (*α* = 0.74–0.80), and secondary traumatic stress (*α* = 0.86–0.89) [47].

The Evidence-Based Practice Attitude Scale (EBPAS-36) is a 36-item questionnaire derived from the EBPAS-50. It assesses the attitudes of mental health providers towards the adoption of evidence-based practice [48]. The measure has been well validated [48].

As “Mein Weg” trainers also work as professionals in CYWS facilities, they will be asked to complete the Implementation Climate Scale (ICS). It measures the degree to which the organizational climate is supportive of evidence-based practice implementation [49]. High internal consistency has been confirmed for the total scale (*α* = 0.91), and for the subscales (*α* = 0.81–0.91).

#### Measures for translators

All participants in the TF-CBT specific translator training will complete measures at four time points: before and after training and 6 and 12 months post-training. They include an evaluation of the translator training (14 items), experiences and attitudes towards translating in mental health contexts (41 items), and the PTSD Checklist for DSM-5 (PCL-5) [50].

### Methods against bias

Random allocation of facilities and participants is ensured by the trial design. All training sessions will be highly standardized and treatment fidelity will be ensured by ongoing case consultations and by session checklists in both interventions. The blinding of UYRs is not possible. All outcomes on the patient level will be well-established measures. Data records will be kept as up-to-date as possible by means of online symptom monitoring and documentation of treatment sessions.

### Data management and storage

Data will be directly entered in an online assessment tool by the relevant informant. Data collected using the paper-pencil procedure will be entered in the same database by an independent data manager. As almost all data will be directly entered in the database, no source data verification will be needed. Incoming data will be continuously monitored and checked for plausibility, quality, and completeness by an independent data manager installed at the University Clinic Ulm. All data will be stored and transferred in pseudonymized form. All the main participants and the IT company responsible for the assessment tool of the trial have signed and followed a data protection concept in accordance with the General Data Protection Regulation (EU) 2016/679 (GDPR). Only authorized and trained study personnel will receive a login-roll in line with their task (e.g., research assistant to start screening, data manager for query management, data entry, data validation, and plausibility checks). For the purpose of long-term storage, the original, pseudonymized data (after database lock) will be stored at the University Clinic Ulm and with the relevant project partners. They will be made available on request to scientific colleagues after the publication of the results.

### Statistical analysis

We will analyze the primary outcome (CATS-2 severity score) using hierarchical linear mixed (HLM) models to account for the nesting of cases within clusters. Mixed effect models, with fixed effects of group (BETTER CARE vs usual care+) and time (intake (T0) versus 6 months (T1) versus 12 months (T2)) as well as their interaction, will be conducted. Primary outcome analysis will be based on the ITT sample (*N* = 540 participants) as the mixed model approach will take missing data and different numbers of reassessments per participant/patient into account. A significance level of *α* = 0.05 will be used. We will also use exploratory mixed linear models to examine the impact of other variables (gender, age, nationality, asylum status) on our primary outcome. Separate (hierarchical) linear mixed models will be used to analyze the secondary outcomes.

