### Trial design

The current study is a cluster randomized controlled hybrid implementation-effectiveness trial with two active conditions (BETTER CARE versus usual care+). An independent institution (Institute of Epidemiology and Medical Biometry, Ulm University) will perform the randomization of clusters (CYWS facility and one therapist for 10 UYRs), stratified by the number of UYRs in the respective CYWS facility (≤ 20 UYRs = small, > 20 UYRs = big facility). Randomization will be done as stratified block randomization with permuted block length using the randomization software ROM [25]. Clusters will be randomized in either BETTER CARE or usual care+ after agreement to participate in the study, after attendance by CYWS staff in the initial information workshop, and after screening (T0) of participants of the respective facility is completed. Selection bias will be avoided by the large number of clusters (*N* = 54). See Fig. 2 for participant flow through the study.

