### Sample size

The sample size calculation was based on a two-step procedure due to the hierarchical data structure. First, we calculated the sample size for an individual randomized study based on our previous data. We assumed a small effect size (ES) of *d* = 0.2 for “Mein Weg” as this intervention is implemented with a non-clinical sample and a medium ES of *d* = 0.5 for TF-CBT. The latter ES reflects the fact that our previous trial with *d* = 1.08 (CATS [19]) was uncontrolled, and treatment was provided in a university setting with highly experienced therapists. We plan to compare BETTER CARE with usual care+ and expect a small effect (*d* ≥ 0.30) in favor of BETTER CARE at 12 months (T2) on the CATS-2. A power analysis for a t-test with independent samples (α = 0.05, two-tailed, power 0.80) results in a minimum sample size of 2 × 176 participants (352 in total). The second step will factor in the cluster structure of the data with participants nested within CYWS facilities/therapists clusters. We assume that each CYWS facility will recruit on average *n* = 10 participants. The design effect is needed for the inflation of the group sample size: DE = 1 + (*m* − 1) × ICC with the fixed cluster size *m* and the intra-cluster correlation coefficient ICC. For the fixed cluster size, a value of *m* = 8 was set because of an estimated dropout rate of 20% of participants (UYRs). For the ICC, a liberal value of 0.05 was assumed to control for the correlation of the outcome of participants living in the same facility. In this context, the DE is 1 + (8–1) × 0.05 = 1.35 which results in a group size of 352 × 1.35 = 476 participants. As every facility recruits 10 participants on average, 48 facilities are needed for the whole trial. With an assumed dropout rate of 10% of facilities, an oversampling of 6 facilities is needed, resulting in 54 facilities (= 2 × 27 facilities). Thus, the overall participant sample within these facilities is estimated as 54 × 10 = 540 participants.

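### The facility-size stratum used in randomisation is missing from the stated fixed effects of the primary model; if size is prognostic, the reported standard error is somewhat too large and the test conservative

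*Protocol article*

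**What the plan says.** Under Trial design, the unit of randomisation is the cluster. "Randomization will be done as stratified block randomization with permuted block length", and the allocation is "stratified by the number of UYRs in the respective CYWS facility", with two levels split at 20.

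Under Statistical analysis, the primary model is a hierarchical linear mixed model "to account for the nesting of cases within clusters". Its fixed part is given as "Mixed effect models, with fixed effects of group (BETTER CARE vs usual care+) and time" (T0, T1, T2), "as well as their interaction, will be conducted". Separate exploratory models will "examine the impact of other variables (gender, age, nationality, asylum status) on our primary outcome". Facility size appears in neither list.

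Under Sample size, the calculation is an independent-samples t-test ("two-tailed, power 0.80") for an effect of d = 0.30 "in favor of BETTER CARE at 12 months (T2) on the CATS-2", inflated by a design effect of 1.35. It takes no credit for stratification.

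**The concern.** A trial is normally analysed with the factors that restricted its randomisation. Here the restriction acts on whole facilities. A facility random effect does not stand in for the stratum: it absorbs any size-related differences into the between-facility variance, as if the arms were free to differ on size. Stratified allocation keeps the arms similar on size, so the group effect truly varies less than the model reports. If facility size predicts CATS-2, intervals come out too wide and the real type I error falls below 5%.

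At stake is some power, in a trial with about fifty clusters. Leaving the term unstated also leaves open a later choice between adjusted and unadjusted results.

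**Working it through.** **1. The plan's own figure.** An exact t-test for d = 0.30 needs 176 per arm (power 0.801), or 352. DE = 1 + (8 − 1) × 0.05 = 1.35. 352 × 1.35 = 475.2, rounded up to 476. 476/10 gives 48 facilities, 48/0.9 = 53.3 gives 54, and 54 × 10 = 540. Every stated figure reproduces, and none depends on the stratum.

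**2. Inputs for the check.** From Sample size: ICC 0.05, m = 8 analysed per facility, d = 0.30 with outcome SD 1, two-sided α = 0.05, and 48 or 54 facilities (K). Assumed: f, the share of between-facility variance explained by size, and two strata of equal size. The article gives no value for f.

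**3. Comparison of 12-month levels.** Normal approximation:

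- Variance that the model without the stratum reports: (4/K) × (0.05 + 0.95/8) = (4/K) × 0.16875.
- True variance under stratified allocation, which is also what the model with the stratum reports: (4/K) × [0.05(1 − f) + 0.95/8].
- Ratio of reported to true standard error: √(0.16875 / [0.05(1 − f) + 0.11875]).
- Actual type I error without the stratum: 2 × [1 − Φ(1.96 × ratio)].
- Power with the stratum: Φ(0.3/SE_true − 1.96).
- Power without it: 1 − Φ((1.96 × SE_reported − 0.3)/SE_true).

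| f (assumed) | Bracket | Reduction in reported variance | Reported SE too large by | Actual type I error | Power without → with, K = 48 | Power without → with, K = 54 |
|---|---|---|---|---|---|---|
| 0% | 0.16875 | 0% | 0% | 0.050 | 71.6 → 71.6% | 76.5 → 76.5% |
| 10% | 0.16375 | 3.0% | 1.5% | 0.047 | 71.9 → 72.8% | 76.9 → 77.8% |
| 20% | 0.15875 | 5.9% | 3.1% | 0.043 | 72.2 → 74.2% | 77.2 → 79.0% |
| 40% | 0.14875 | 11.9% | 6.5% | 0.037 | 72.8 → 76.9% | 77.9 → 81.5% |

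Example for f = 40%, K = 54: SE_reported = √(4/54 × 0.16875) = 0.1118 and SE_true = √(4/54 × 0.14875) = 0.1050. The ratio is 1.065. Power with the stratum is Φ(2.858 − 1.960) = 0.815.

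The gain is about 1, 2 or 4 points. Power without the stratum also rises with f, because the allocation lowers the true variance whether or not the stratum is modelled.

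**4. Interaction contrast (T2 minus T0).** In the stated model T0 is a response, so a size effect that is constant over time cancels from this contrast.

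- A generalised-least-squares calculation used 48 facilities of 10, ICC 0.05, about 20% dropout by T2, facility and person random intercepts, and residual variance 0.5 (assumed). The standard error of the group-by-T2 term was 0.09790 without a stratum main effect. With it, the value was 0.09790 at f = 10% and 20%, and 0.09789 at f = 40%.
- In a simulation with 54 facilities of 8 (5,000 runs per scenario; correlations over time assumed 0.5), the unadjusted change analysis kept type I error at 5.3% for f = 20% and 5.5% for f = 50%, with Monte Carlo error of about 0.6 points.

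A stratum main effect alone therefore does nothing useful for this contrast. A stratum-by-time term is needed, and it helps only if size predicts change.

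**The case against.** The best counter-argument is that this is a condensed article, that its analysis plan is not shown, and that the text never says its list of fixed effects is complete. The random-effects structure is not spelled out either. That tempers the point, and the unseen plan may already contain the stratum. It does not remove the point: the section gives a concrete fixed part and a separate covariate list, and the randomisation factor is in neither.

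Second, nothing in the article shows that facility size predicts CATS-2. This stands; with f = 0% there is nothing to gain.

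Third, the figures for a 12-month level comparison do not carry over to the interaction contrast. This also stands, so the gain is conditional. The level comparison is still relevant, because Primary outcome names CATS-2 at 12 months and Sample size powers a two-group comparison at T2.

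A reader might infer that the precision bought by stratification is thrown away, or that the true variance of the group effect would fall by 3%, 6% or 12% once the stratum is added. Neither follows. Those percentages describe the variance that the model reports; the estimate already has the benefit of balanced allocation.

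**Conclusion.** The point holds in a limited form. The stated fixed effects leave out the factor by which clusters are randomised. If size is prognostic, the cost for a 12-month level comparison is a standard error about 1.5% to 6.5% too large and about 1 to 4 power points, for an assumed 10% to 40% of between-facility variance, ICC 0.05, 8 analysed per facility and equal strata. At 0% the cost is nil. For the T2-minus-T0 contrast it is near nil unless size predicts change.

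Any error is conservative: no bias and no inflated type I error. It would be wrong to blame this omission for the baseline powers below 80% in the table. Those arise because 476 is divided by 10 recruited per facility while 8 are expected at follow-up, which is a separate matter. Severity is minor.

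**What to change.** State in the primary model, and in the secondary-outcome models, that the randomisation stratum (facility size as classified at randomisation) and stratum by time enter as fixed effects, so that the 12-month group contrast is adjusted for the stratum. If the stratum is left out on purpose, say why.

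The stratum is known for every randomised facility, so no data need be collected. The price is about one cluster-level degree of freedom per term, out of about 46 with 48 facilities (48 − 2) or 52 with 54 (54 − 2). The sample-size section needs no change on this account.

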**Methods:**

In a cluster randomized controlled trial involving *N* = 540 UYRs living in up to *N* = 54 child and youth welfare service (CYWS) facilities, BETTER CARE will be compared with usual care+. We will randomize clusters comprising a CYWS facility with at least one eligible psychotherapist. BETTER CARE consists of step (1) screening and indication and either step (2) preventive trauma-focused group intervention “Mein Weg” delivered by trained CYWS staff or step (3) TF-CBT delivered by trained community therapists and supported by trained translators if necessary. Participants will be assessed 6 and 12 months after randomization. The primary outcome is the severity of PTSS after 12 months. Secondary outcomes are depressive and anxiety symptoms, quality of life, and proxy reported PTSS. Furthermore, drug use, health costs, benefits, and long-term effects on integration/acculturation will be assessed.

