#### Primary outcome

The CATS-2 [26] at the 12-month follow-up is the primary outcome. The first part consists of an event checklist with 15 items to be answered yes/no. The second part consists of 20 items corresponding directly to PTSD criteria according to the Diagnostic and Statistical Manual of Mental Disorders 5 (DSM-5 [29]) They measure the severity of PTSS employing a 4-point scale ranging from 0 (never) to 3 (almost always). To evaluate psychosocial functioning, five dichotomous items (yes/no) investigate whether the rated PTSS interfere with key areas of functioning. Good internal consistency (*α* = 0.75–0.93) has been confirmed in the initial validation [26] and in an RCT with UYRs (*α* = 0.75) [12]. At present, the CATS is accessible in several languages and has been successfully used in previous studies with UYRs [2, 19]. For the current study, a slightly adapted version (CATS-2) will be used to cover ICD-11 PTSD and complex PTSD criteria in addition.

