#### Exploratory outcomes

The primary and secondary outcomes will be analyzed in an exploratory manner at the 6-month follow-up.

The Alcohol Use Disorders Identification Test (AUDIT) is a 10-item questionnaire used to assess recent excessive drinking and is in conformity with ICD-10 definitions [35]. It is a well-validated (α = 0.80–0.94) [36] measure of risk across gender, age, and cultures.

The Cannabis Use Disorder Identification Test, Revised (CUDIT-R) is an 8-item questionnaire used to assess cannabis use disorder severity [37]. The CUDIT-R has been validated (*α* = 0.91) as both a screening test and a rating scale for cannabis use disorder severity [37].

The EQ-5D-3L [38] is a two-part instrument for the definition and the valuation of health states as the basis for the estimation of quality-adjusted life years (QALYs). It consists of a descriptive part and a visual analog scale similar to a thermometer [39]. At present, the EQ-5D-3L is available in more than 180 languages including all those expected to be relevant for the project.

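### The primary model leaves the pre-randomisation baseline difference free and ties no term to the 12-month endpoint, so any 12-month contrast taken from it is less precise than it could be

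*Protocol article*

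**What the plan says.** The protocol article fixes the primary time point several times. In the abstract, "The primary outcome is the severity of PTSS after 12 months". Under Primary outcome, the CATS-2 "at the 12-month follow-up is the primary outcome". The Sample size section expects d of at least 0.30 "in favor of BETTER CARE at 12 months (T2) on the CATS-2" and rests on this: "A power analysis for a t-test with independent samples", two-sided at 0.05 with 80% power. Under Exploratory outcomes, "The primary and secondary outcomes will be analyzed in an exploratory manner at the 6-month follow-up".

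The Statistical analysis section then describes a hierarchical linear mixed model with fixed effects of group and "time (intake (T0) versus 6 months (T1) versus 12 months (T2)) as well as their interaction, will be conducted". It sets alpha at 0.05 and uses an intention-to-treat sample of 540. It does not say which term or contrast answers the primary question. Baseline CATS-2 is not a covariate, and it is not among the variables listed for the exploratory models. The Trial design section says that a facility is randomised only once its T0 screening is complete.

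**The concern.** Two features of the stated model fit poorly with the stated endpoint.

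- **Free baseline.** Intake is one of the three time levels, with group and group-by-time terms, so the model estimates a group difference at T0. Because T0 precedes randomisation, that difference is zero in expectation. Estimating it freely gives up precision that a baseline measured on every participant could provide.
- **No named contrast.** The model yields several tests: the T2 group difference, the T2-by-group coefficient (a difference in change from T0), and a joint 2-df interaction. They differ in precision and can disagree. The joint test would also bring in T1, which the protocol calls exploratory.

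At stake is power for the primary comparison, in a trial whose Strengths and limitations section already warns that recruitment may be difficult.

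**Working it through.** **Plan's own figure.** For d = 0.30, two-sided alpha 0.05 and 80% power, the exact t-test solution is 175.4, so 176 per arm and 352 in total. Then 352 × 1.35 = 475.2, so 476; 476/10 = 47.6, so 48 facilities; 48/0.9 = 53.3, so 54; and 54 × 10 = 540. The stated figures reproduce.

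**Variance factors.** Assume complete data and equal variance at T0 and T2, and let r be the T0–T2 correlation of the scores analysed. Relative to a plain T2 comparison:

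- T2 difference with free baseline: 1
- T2-minus-T0 difference in change: 2(1 − r)
- T2 difference with baseline constrained or adjusted: 1 − r²

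Since 1 − r² = (1 − r)(1 + r), the last factor is at most 1 and at most 2(1 − r). The ordering therefore needs no value of r.

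**Inputs for power.** From Sample size: 48 facilities after facility dropout, 8 completers each after 20% participant dropout, ICC 0.05, d = 0.30. So 48 × 8 = 384 completers, DE = 1 + 7 × 0.05 = 1.35, and in SD units SE = √(4 × 1.35/384) = 0.1186. Power = Φ(0.30/(0.1186 × √factor) − 1.96). The document does not give r, so it is assumed; here it is the correlation of cluster-mean scores.

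| Assumed r | T2 only | Difference in change (factor) | Baseline constrained (factor) |
|---|---|---|---|
| 0.4 | 72% | 64% (1.20) | 79% (0.84) |
| 0.5 | 72% | 72% (1.00) | 83% (0.75) |
| 0.6 | 72% | 81% (0.80) | 89% (0.64) |

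T2-only power is 72% here, not 80%, because 384 completers fall short of the 476 that the design effect requires. That is a separate matter.

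**Same comparison at the plan's 176 per arm, before clustering.** T2-only power is 80%. For a participant-level r of 0.3/0.4/0.5/0.6/0.7/0.8, the difference in change has 66/73/80/88/95/99% and the constrained contrast 84/87/90/94/98/99.7%.

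**Where the change contrast matches the T2 test.** Setting 2(1 − r) = 1 gives r = 0.5 for the scores analysed. With clusters of 8 and ICC 0.05, the cluster-mean correlation is [0.05c + (ρ − 0.05c)/8]/(0.05 + 0.95/8), where ρ is the participant-level correlation and c the correlation of the facility effects over time. Setting this to 0.5 gives ρ = 0.325 for c = 1.0, 0.395 for c = 0.8 and 0.50 for c = 0.5. Break-even therefore lies at ρ of about 0.3 to 0.5.

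**Joint interaction, if it were used.** At 176 per arm with a T1 effect half the T2 effect, the 2-df test has 56/71/91% power at r = 0.3/0.5/0.7, against 80% for the T2 t-test. It can be the weaker or the stronger test.

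**The case against.** The strongest reply is that the section lists model terms and names no test. The T2 group difference can be read from the same model as the group effect plus the T2 interaction term. With complete data and an unrestricted covariance, that is essentially the comparison used for planning. Other sections already make 12 months primary and 6 months exploratory, and an analysis plan that is not shown may name the contrast.

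Much of this stands, and it rules out three stronger readings that a reader might infer:

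- **That the primary test is the interaction, so significance could rest on T1 alone.** No sentence says so, and a confirmatory claim on T1 would contradict the Exploratory outcomes section.
- **That the analysis is less powerful than planned.** This holds only for the difference in change, and only below the break-even correlation. Above it, the change contrast beats the planned t-test.
- **That the analysis is biased or inflates type I error.** T0 precedes randomisation, so the listed model still gives an unbiased contrast, and nothing here shows an error rate above 0.05.

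What the reply does not remove is the free baseline, which is written into the model. Even on the most favourable reading, the T2 difference has factor 1 where 1 − r² is available.

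**Conclusion.** The point holds as one of avoidable inefficiency and an untied primary contrast. Both single-degree-of-freedom T2 contrasts that the stated model offers are less precise than a baseline-constrained one whenever r lies strictly between 0 and 1. At an assumed cluster-mean r of 0.4 to 0.6, constraining the baseline cuts the variance by 16% to 36% against T2 alone, worth about 7 to 17 points of power. Against the difference in change, the ratio (1 + r)/2 means a cut of 30% to 20%, worth about 15 to 8 points.

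The ordering is general under the assumptions stated above. The sizes rest on the protocol's own ICC, dropout and effect size and on a correlation that it does not give. This is an improvement available at no cost; the planned analysis is not invalid.

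**What to change.** In the Statistical analysis section, name one primary test: the 1-df BETTER CARE minus usual care+ contrast in CATS-2 at T2. Take it from a mixed model for T0, T1 and T2 that constrains the T0 means to be equal across arms, keeping the facility effect and the within-participant correlation. Report the T1 contrast and any joint interaction as exploratory.

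The constrained model is preferable to one with T1 and T2 as outcomes and T0 as a covariate. The two are not identical when data are missing: the covariate model drops participants who have only T0, whereas the constrained model keeps them in the intention-to-treat sample.

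The cost is a change of wording in the protocol or analysis plan, best made before outcome data are seen. It needs no new data and no extra participants.

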## Background

Refugee minors often arrive in European host countries without their parents or other caregivers. In Germany, unaccompanied refugee minors have the possibility to remain in the care of child and youth welfare services (CYWS) up to the age of 21. We, therefore, use the terms minors and young adults when referring to unaccompanied young refugees (UYRs). However, there are reports that CYWS staff have been confronted with major challenges, for instance, limited professional experience and insufficient training [1]. A recent cross-sectional study showed that UYRs in southern Germany had experienced a high number of traumatic events, and presented elevated levels of posttraumatic stress symptoms (PTSS), depression, and anxiety [2]. Symptoms, especially within the re-experiencing cluster, seem to be central in this population [3], and they differ in this respect from other traumatized children and adolescent samples [4]. These findings are in line with several studies from other European countries reporting high PTSS rates from 20% [5] to 76% [6]. On average, symptoms tend to be stable over time [7] even though another recent study by Müller et al. [8] indicated a significant reduction in PTSS severity after 12 months. However, the rates for clinically relevant PTSS (38%) were still high. Additionally, UYRs often suffer from ongoing stressors in their host countries, so-called post-migration stressors, such as worries about their families or acculturation distress [9].

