#### Criteria for participants

Inclusion criteria for participants are (1) age 12–20 years; (2) arrived in Germany as unaccompanied minors; (3) applied for asylum or intend to do so; (4) being cared for by a CYWS facility at screening; (5) written informed consent given by participant and legal guardian (if < 16 years at screening); and (6) reported at least one traumatic event in line with the DSM-5 A criterion. No exclusion criteria have been defined for participants in the RCT.

If they are to be referred to and treated with TF-CBT in the event of randomization to BETTER CARE, UYRs have to meet the following criteria: (1) a score (self-report) of ≥ 25 points in the initial screening with the Child and Adolescent Trauma Screen, second version (CATS-2) [26]; and (2) diagnosis of PTSD (according to International Classification of Diseases 10 [ICD-10]) or any mental disorder (ICD-10) as confirmed by the therapist. Exclusion criteria for TF-CBT treatment are (1) acute danger to themselves or others; (2) acute psychosis; (3) acute suicidality; (4) severe substance abuse; or (5) severe mental disability (each as judged by the therapist). Study participants who were excluded from the study will be referred to a more appropriate treatment for their needs, such as inpatient mental health care institutions.

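### Age is left out of the primary model that is meant to absorb missing data, although age-related loss by 12 months is plausible; adding age and age × time is a nearly free safeguard of modest impact

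*Protocol article*

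**What the plan says.** The Statistical analysis section of the protocol article specifies "Mixed effect models, with fixed effects of group (BETTER CARE vs usual care+) and time", plus their interaction, with nesting in clusters. It bases the primary analysis on all 540 participants, on the ground that a mixed model accommodates missing data and unequal numbers of reassessments. Age is named there, but only for "exploratory mixed linear models to examine the impact of other variables", together with gender, nationality and asylum status.

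Four other places bear on who is still observed at month 12:

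- Criteria for participants: entry at 12 to 20 years. The care criterion is "being cared for by a CYWS facility at screening", with no requirement that care continue.
- Background: unaccompanied refugee minors in Germany can "remain in the care of child and youth welfare services (CYWS) up to the age of 21".
- Study setting and recruitment: assessment is located in the facilities, private practices and outpatient clinics.
- Trial design and Procedure: T0 precedes randomization and T2 is 12 months after it.

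The Sample size section gives one dropout figure for participants, 20%, not split by age or arm.

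**The concern.** T0 comes before randomization and T2 comes 12 months after it, so everyone aged 20 at T0 has turned 21 by T2 and has reached the upper age of care. Where assessment is organised through the facility, the oldest participants may be the hardest to reach.

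A likelihood-based mixed model handles missing outcomes correctly if, given the covariates and observed scores in the model, missingness does not depend on the unobserved scores. If age influences both the chance of being seen at T2 and the CATS-2 score, leaving it out weakens that condition. The T0 and T1 scores carry only part of the age information.

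The arms could differ in whom they keep: only BETTER CARE refers participants to study therapists. If it retained more of the older youths and older youths scored differently at T2, the group × time contrast would mix treatment effect with age composition, although the variable needed to separate them is on file.

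**Working it through.** **Yardstick.** The planned effect is d = 0.30 at T2 ("α = 0.05, two-tailed, power 0.80"). The stated sample size reproduces: 175.4 per arm by t-test, so 176, giving 352. The design effect is 1 + 7 × 0.05 = 1.35, and 352 × 1.35 = 475.2, so 476. That is 48 facilities; 48 / 0.9 = 53.3, so 54, and 54 × 10 = 540. Bias is expressed below as a share of 0.30.

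**Assumed inputs (none is in the article).**
- Ages uniform on 12 to 20: mean 16, variance (81 − 1)/12 = 6.67, and 2/9 of participants aged 19–20 (mean 19.5; the rest average 15).
- Loss of 10% below age 19. T1 and T2 are lost together.
- Within-person correlation 0.55 given age; person plus residual variance 1.
- Age slope at T2 of s = 0.05 to 0.10 SD per year, older youths scoring higher.

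**Step 1: age of those observed at T2.** If a fraction q of the 19–20 group is lost, their share among those observed is w = (1 − q)(2/9) / [(1 − q)(2/9) + 0.9 × 7/9], and the mean age is 15 + 4.5w. For q = 0.30, w = 0.1556/0.8556 = 0.182 and the mean is 15.82. For q = 0.80, w = 0.0444/0.7444 = 0.060 and the mean is 15.27. The gap is Δ = 0.55 years. The other rows follow in the same way.

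**Step 2: bias without age.** The model carries over the part of the age effect visible at T0, with regression coefficient β. So bias ≈ Δ × (s at T2 − β × s at T0).
- Stable age effect: Δ × s × (1 − β), with β = (0.55 + 6.67s²)/(1 + 6.67s²). This is 0.557 at s = 0.05 and 0.578 at s = 0.10.
- Age effect absent at T0 and reaching s by T2: Δ × s.

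| Loss at 19–20, usual care+ vs BETTER CARE | Δ (years) | Stable effect, s = 0.05 to 0.10 | Growing effect, s = 0.05 to 0.10 |
|---|---|---|---|
| equal | 0 | 0 | 0 |
| 70% vs 30% | 0.43 | 0.009 to 0.018 | 0.021 to 0.043 |
| 80% vs 30% | 0.55 | 0.012 to 0.023 | 0.027 to 0.055 |
| 90% vs 20% | 0.77 | 0.017 to 0.033 | 0.039 to 0.077 |

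With a true effect of −0.30, the 80% vs 30% growing case at s = 0.10 gives about −0.245, a loss of 0.055/0.30 = 18%, or roughly 20%. Large-sample likelihood simulation under these inputs agrees to within 0.01 SD and returns about −0.30 once age × time is included. The sign follows the age slope: if older youths score lower, the effect is overstated.

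**Step 3: a milder finite-sample case.** With 54 facilities of 10, ICC 0.05, loss at T2 only (20% in each arm), 70% vs 30% at ages 19–20 and a stable age correlation of −0.1, −0.2 or −0.3, the bias was −0.006, −0.011 and −0.018 SD without age, and 0 to −0.002 with age.

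**Step 4: precision.** The standard error of the group × time contrast at T2, from person-level random-intercept models (25 simulated trials, no facility term), was 0.0887 without age, 0.0886 with an age main effect and 0.0888 with age × time. A stable age effect cancels in change from T0.

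**The case against.** The strongest reply is that the two facts actually documented, entry to 20 and care to 21, point at most to age-related loss, and age-related loss that is equal in both arms leaves the contrast unbiased. No passage indicates an arm-specific gradient. The therapist-tie mechanism is conjecture: only those scoring 25 or more are referred to TF-CBT, and the ethics section lets participants stay with their therapist after leaving the research. The 80% vs 30% scenario also implies overall loss of 25.6% vs 14.4% (1 − 0.7444 and 1 − 0.8556), an imbalance that the article does not suggest. If T1 is fully observed, a stable age effect under similar loss rates gives only 0.007 to 0.015 SD. A randomized comparison without age is a standard analysis, and further covariates or sensitivity analyses may sit in a plan not shown. All of this stands. It limits the size and priority of the point, but the article itself fixes the primary fixed effects and assigns age elsewhere.

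Three stronger readings are tempting and unsupported:

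- A reader might infer that the care rules make 12-month loss depend on age by design. They do not. Self-report can be done on tablet or paper, each assessment is paid, and a subsample is followed to 24 months. Age-related loss is an inference.
- A reader might expect age to sharpen the estimate. For this contrast it does not (Step 4).
- A reader might expect the fix to cover a treatment effect that varies with age. With equal loss and an effect changing by 0.1 SD per SD of age, the estimate without age was −0.284 against −0.300, an age main effect still gave −0.285, and only letting age act separately by arm recovered it (−0.298).

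**Conclusion.** The point holds as a low-priority improvement. The primary model omits a collected baseline variable that may be related to being observed at T2, while the analysis leans on that model for missing data. The T2 contrast is biased only if age-related loss differs by arm and CATS-2 level or course depends on age. Under the assumed inputs the bias is zero with equal loss, about 0.01 to 0.03 SD (3% to 10% of 0.30) with a stable age effect, and up to about 0.06 SD (20%) with a growing age effect and 80% vs 30% loss; the extreme 90% vs 20% case reaches about 0.08 SD. Against a standard error near 0.089, most of these are small. The age distribution, loss by age and arm, age slope and within-person correlation are all assumptions. The conclusion is that conditioning on age makes the missing-data assumption easier to defend, not that the planned analysis is invalid.

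**What to change.** In the Statistical analysis section, prespecify age at T0 (continuous) and age × time as fixed effects in the primary model. Keep the model without age as a sensitivity analysis, and leave gender, nationality and asylum status exploratory. State that this addresses age-related missingness and is not a test of effect modification.

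The cost is one sentence and two degrees of freedom beyond the age main effect (three visits), with no new data and no more participants. At manuscript submission no facility had been randomized and no participant screened (Trial status), so the choice could then be made without sight of outcomes. If the trial has moved on, fix it in a dated amendment or analysis plan before outcome data by arm are examined.
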